### Recruitment

2.14

All participants in this trial will be recruited from the outpatient and inpatient of the Second Affiliated Hospital of Heilongjiang University of Chinese Medicine, and we also plan to recruit through the hospital website and Wechat official account. During the recruitment process, posters, pictures, and videos related to the study will be produced to help participants understand the purpose of this study, explain the advantages, disadvantages and effects of treatment, and inform participants what they need to do to participate in this study. According to the inclusion/exclusion criteria, we will conduct a preliminary assessment to determine and screen whether the following may be included: participants who are interested in participating in the study, and based on the test results to determine whether they can further participate in the study. Subjects who meet the inclusion criteria will be informed of the details of the trial, and subjects or their legal guardians will be required to sign an informed consent form before treatment. The recruitment of subjects is expected to begin on September 1, 2021 and end in March 2023. It may be completed ahead of schedule if a sufficient number of patients are recruited.

### Informed consent

2.15

Before the study, the general research process will be explained at the time of participant recruitment. Participants will be informed that participation in the trial is absolutely voluntary and that they can withdraw from the trial at any time. In the case of withdrawal, the collected participant study data will not be deleted and will be used for final analysis. Each participant should obtain and sign written informed consent before receiving any intervention related to this study.

### Randomization and allocation

2.16

All VCI patients with T2DM will be randomly divided into 2 groups: the experimental group and the control group according to the order of case visit and admission. A specialized statistical analyst who is not a researcher in this study will be entrusted to use PASS15.0 software to generate random-number sequences for randomization. Strips identifying participants by grouping information will be hidden in sealed opaque envelopes with sequential numbers. The envelopes will not be opened until informed consent is obtained. All cases were screened with strict reference to the inclusion and exclusion criteria, and the patients who met the inclusion criteria were randomly selected and grouped by computer until the total number of patients (30) was reached. The cases of healthy volunteers and T2DM patients with normal cognitive function were selected into the group according to the order of medical treatment until the total number of patients (25) was reached. A professional statistician who is not a researcher in the study will produce the distribution order. Participants will be recruited by an independent researcher and assigned to different interventions.

### Blinding

2.17

Due to the limitations of this protocol and the particularity of acupuncture and cognitive treatment, we were unable to adopt a double-blind study design. However, outcome evaluators and statistical analysts may not know the grouping, so they can be blinded. With the exception of the evaluation process, the outcome evaluators will not contact any participants. In the process of data management and statistical analysis, we will invite independent professionals to handle data management, and the statistical analysis of all data will be performed by professional statisticians who are not the principal researchers. Therefore, this will be a partial randomized controlled trial that blinds the evaluators and statistical analysts of the results.

### Intervention

2.18

All acupuncture physicians and rehabilitation therapists in this trial have at least 3 years of working experience. Participants in different groups will receive different treatments 6 times a week for 12 weeks. The specific intervention methods are as follows:

Healthy volunteers (HC group): without any intervention.

**T2DM with normal cognitive function group** will be given routine blood glucose control drugs, and anti-platelet aggregation, blood pressure control, and lipid control were given according to patients with different complicated diseases.

**VCI with T2DM group**: the control group was only given routine blood glucose control and cognitive function improvement drug (donepezil 5 mg, once a day, orally), and symptomatic treatment was given according to patients with different complicated diseases. On the basis of the control group, the experimental group was treated with acupuncture-rehabilitation therapy; the specific method is to carry out dual task executive function training was conducted during the period of acupuncture retention at the cluster needling at scalp points.

### Cluster needling at scalp points^[7]^

2.19

The acupoints were taken from the parietal region, anterior parietal region, and frontal region in the 7-zone division method, the parietal area (from Baihui to Qianding and its 1-inch and 2-inch parallel lines to the left and right respectively), the anterior parietal area (from Qianding to Xinhui and its 1-inch and 2-inch parallel lines to the left and right respectively), and the frontal area (from Shenting to Xinhui, and its 1-inch parallel lines to the left and right, respectively).

Method of operation: the method of keeping the needle for a long time and sewing intermittently is adopted. After conventional disinfection, the acupoint was punctured from front to back according to the above-mentioned acupoint area, and the acupuncture point was quickly punctured at an angle of 30 degreeto the skin, followed by a slow acupuncture under the cap aponeurosis at an angle of 15 degree to the skin, and about 30 mm was inserted into the needle body. After the needle was twisted, 200 times per minute, each needle was twirled for 1 minute, and the needle was retained for 6 to 8 hours. During the needle retention period, start twirling once every 30 minutes, repeat twice, and then twirl once every 2 hours until the needle comes out. The patients were treated 6 days a week for 12 weeks. Figure 2*presents the Cluster needling at scalp points.*

**Figure 2 F2:**
[figure not shown]
present the Cluster needling at scalp points.

### Dual-task executive function training

2.20

In the first task “nailboard test,” the subjects were asked to insert the wooden nails into the holes in the board sequentially with the affected hand within 30 seconds, and the average number of nails inserted three times was recorded. The second task “continuous minus 7,” selects from the data card marked 290–310 randomly, displays the selected initial data at the beginning of the nailboard test, counts backward with 7 as a unit, records with a recording pen, and timing with a timer, carries out a single continuous minus 7 task and a dual task minus 7, respectively, and records the correct number of responses within 30 seconds (all the data correctly minus 7 by the previous data are regarded as a correct calculation). The number of 3 reactions was recorded and the average value was taken. The patients were treated 6 days a week for 12 weeks.

### Outcome measures

2.21

All participants will be were evaluated for serum biological indicators and neuropsychological scales before treatment, 4 weeks of treatment, 8 weeks of treatment, and 12 weeks after treatment. fMRI scans were performed before treatment and 12 weeks after treatment. All treatment evaluations will be conducted by researchers who will be blinded to the treatment allocation.

### Basic characteristic variables

2.22

All of the participants’ general status demographic information such as age, sex, educational background, marital status will be attained from baseline questionnaires. Vital signs (pulse, respiration rate, temperature, and blood pressure) will be measured by nurses.

### Primary outcome measurement

2.23

**VBM:** The VBM is an automatic, comprehensive and objective analysis technique for magnetic resonance imaging (MRI) of brain structures based on voxels. VBM can be noninvasively and accurately study the morphology of living brain and reflect the difference of corresponding anatomical structure by analyzing the changes of each voxel. It is a reliable method to evaluate gray and white matter lesions and plays an important role in the diagnosis of diseases related to cognitive impairment.

**SOD:** The SOD is an active substance derived from living organisms, which can eliminate harmful substances produced by living organisms during metabolism. SOD is mainly used to prevent and treat local cerebral hemorrhage, ulcers, eliminate inflammation, arrhythmia, rheumatism, rheumatoid disease, radiation injury, drug poisoning, and other diseases, and can prevent and treat brain function recognition disorders caused by specific or non-specific brain damage.

**MDA:** The MDA is the final product of lipid peroxide metabolism formed by oxygen free radicals attacking unsaturated fatty acids in biological membranes. It is cytotoxic and can cause cross-linking reactions of DNA, membrane proteins, enzymes, among others, and increase membrane permeability, resulting in changes in the structure, function and metabolism of cell membranes result in damage or death of cells and even the body, which can directly reflect the intensity and rate of lipid peroxidation in the body, and indirectly reflect the content of oxygen free radicals and the degree of nerve cell damage. It is an important biomarker reflecting lipid peroxidation and oxidative stress.

**BDNF:** The BDNF is a protein with neurotrophic effect. It is one of the very important members of neurotrophin family. It was first found in pig brain by Barde et al. Because it can promote the growth, reproduction, regeneration and repair of injured neurons, it mainly has extensive neuroprotective and neurotrophic effects, also is important for neuron survival, maintenance of normal function, and repair after damage. Therefore, it is mainly expressed in the central nervous system, especially in the cortex and hippocampus.

### Secondary outcome measures

2.24

**MoCA Scale:** The MoCA is presently recognized as one of the cognitive impairment screening scales, which mainly includes attention, executive function, memory, speech, visual space structure, abstract thinking, calculation ability, and other aspects of screening.^[8]^ Compared with the MMSE, MoCA has better sensitivity and specificity for mild cognitive impairment. The total score of MoCA is 30 points. If the subject has been in education for ≤12 years, 1 point is added. A score <26 points is considered to have cognitive impairment.

**WMS-IV:** The Wechsler Memory Scale (WMS) is a set of tests to assess various memory abilities and working memory. It can provide detailed evaluation of clinical memory function for patients suspected of having memory deficits, psychiatric diseases, or developmental disabilities. The WMS was released in 1945 and has been revised to the fourth edition(WMS-Fourth edition) in 2008,^[9]^ WMS-IV has adjusted and improved the structure and content of the original scale, extended the age of the subjects to 16 to 90 years’ old, and added 4 subscales (concise cognitive status assessment, graphic recognition, spatial superposition, symbol breadth), and provide auditory memory, visual memory, visual working memory, instant memory and delayed memory, and total memory quotient to explain the individual's memory ability.^[10]^ Not only to assess memory function, but also to make a brief assessment of cognitive function status.

**FIM:** The FIM is a comprehensive and objective assessment method that reflects the patient's activities of daily living. It selects the most common and useful 18 functional assessment items (including 6 self-care activities, 2 sphincter control, 3 transfers, 2 walking, Communicate 2 items and 3 social cognition items), and determine the appropriate grading scoring method (each item is divided into 7 levels, the highest score is 7 points, the lowest score is 1 point, the total score is the highest 126 points, the lowest 18 points. The higher the score, the better the level of independence, the worse on the contrary.). This scale can comprehensively reflect the patient's function and independent living ability, evaluate and compare the severity of the patient's disability, predict the rehabilitation consequences, formulate rehabilitation goals, select treatment plans, and evaluate the rehabilitation efficacy.

### Safety evaluation and adverse events

2.25

The safety evaluation mainly focuses on safety indicators and adverse events. The safety indicators will be tested once before and after the treatment, include general physical examination (blood pressure, breathing, pulse, temperature), routine blood tests, routine urine tests, routine stool tests, electrocardiograms, and liver and kidney function tests. Adverse events in this study will be defined as any discomfort, symptoms, or diseases that occurred during this trial, such as fainting, allergies, or pain. If someone faints, researchers will stop all treatments immediately, then keep the patient in a supine position in a ventilated place, and give him/her warm water or sugar water to let him/her fully rest until the body recovers. If allergies or pain occurs, all treatments will also stop immediately, and the patient will be treated symptomatically. All the above detailed information regarding safety evaluations will be reported in detail in case report forms (CRFs), and the impact of all adverse events will be analyzed at the end of the study. Participants who experience adverse events will be compensated accordingly.

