**Figure 1 F1:**
[figure not shown]
Present the technology roadmap.

**Table 1 T1:** Timing of treatment assessments and data collection.

Research stage	Selection period	Baseline period	Treatment period		
Evaluation times	First time		Second time	Third time	Fourth time
Evaluation times point	1 or 0 day before treatment		4 wk after intervention ± 3 days	8 wk after intervention ± 3 days	12 wk after intervention ± 3 days
Inclusion criteria	×				
Exclusion criteria	×				
Informed onsent form		×			
Random grouping		×			
General assessment					
General information		×			
Present medical history/allergic history		×			
History/complications		×			
Physical check		×	×	×	×
CDR		×			
MMSE		×			
IADL		×			
Evaluation of the curative effect index					
Laboratory examination		×	×	×	×
fMRI scan		×			×
MoCA		×	×	×	×
WMS-IV		×	×	×	×
FIM		×	×	×	×
Security assessment					
Life indication		×	×	×	×
Other assessments					
Drug combination		×	×	×	×
Adverse reactions/events			×	×	×
Treatment compliance			×	×	×

CDR = clinical dementia scale, IADL = instrumental activity of Daily living scale, fMRI = functional magnetic resonance imaging, MMSE = Mini Mental State scale, MoCA = Montreal Cognitive Assessment, WMS-IV = Wechsler Memory Scale IV edition

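### Adverse events cover any discomfort, but only the experimental arm has 72 described treatment sessions at which to notice them, and the last scheduled safety check may precede the final sessions

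*Protocol article*

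**What the plan says.** All references are to the protocol article.

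- **AE definition (section 2.25):** "Adverse events in this study will be defined as any discomfort, symptoms, or diseases that occurred during this trial". Fainting, allergy and pain are given as examples. No threshold of severity or relatedness is stated. Events go into the case report form (CRF), and their impact is to be analysed at the end of the study.
- **AE schedule (Table 1):** the row "Adverse reactions/events" is marked at weeks 4, 8 and 12 under the treatment period. The last column is headed "12 wk after intervention ± 3 days", and no later column follows.
- **Experimental arm (section 2.19):** "The patients were treated 6 days a week for 12 weeks", and at each session "the needle was retained for 6 to 8 hours", with repeated twirling. Section 2.18 adds dual-task training during retention.
- **Control arm (section 2.18):** "the control group was only given routine blood glucose control and cognitive function improvement drug", the latter being oral donepezil once a day, plus symptomatic treatment as needed. No treatment sessions are described.
- **General frequency (section 2.18):** "Participants in different groups will receive different treatments 6 times a week for 12 weeks".
- **Blinding (section 2.17):** treatment is not double-blind. Outcome evaluators and statistical analysts are to be blinded.
- **Safety indicators (section 2.25):** vital signs, laboratory tests and ECG are tested once before and once after treatment.

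**The concern.** A definition that takes in every minor symptom is the kind most sensitive to how often a patient is seen. Staff who know the allocation spend hours with experimental patients six days a week. As far as the article describes it, a control patient is asked about AEs three times, each time looking back about four weeks. A passing headache or an upset stomach could be written down in one arm and forgotten in the other.

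Controls are the only comparator that can separate effects of acupuncture-rehabilitation from effects of the drugs that both randomised arms receive. If capture differs between the arms, a shared drug effect can appear as a procedure effect. This cannot be fully repaired after data collection.

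The second question is whether the last scheduled AE enquiry and safety check can come before treatment has finished.

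**Working it through.** The article states no AE rate, safety margin or safety power, so there is no figure of its own to reproduce.

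**1. Opportunities to record an event.**
- Experimental sessions: 6 per week × 12 weeks = 72 (section 2.19).
- Needle retention: 72 × 6 h = 432 h to 72 × 8 h = 576 h.
- Described contacts: 72 sessions + 3 visits = 75 in the experimental arm, against 3 visits in the control arm. The ratio is 75/3 = 25. It assumes that controls have no other contact, which the article neither states nor rules out.

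**2. Effect of unequal detection (illustration only).** Recorded risk = true risk × detection probability. With equal true risk in both arms, the recorded risk ratio is the ratio of the detection probabilities. All detection values and true risks here are assumptions; n = 15 per arm is from section 2.5. The last column gives the probability of a two-sided Fisher exact p < 0.05, found by enumerating all outcomes, as true risk runs from 20% to 60%.

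| Detection, experimental / control | Recorded risk ratio | Expected recorded patients of 15, true risk 40% | Chance of p < 0.05 |
|---|---|---|---|
| 0.9 / 0.9 | 1.0 | 5.4 vs 5.4 | 1.6% |
| 0.9 / 0.6 | 1.5 | 5.4 vs 3.6 | 2.2% to 7.8% |
| 0.9 / 0.3 | 3.0 | 5.4 vs 1.8 | 5.0% to 37% |

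For example, 15 × 0.40 × 0.9 = 5.4 and 15 × 0.40 × 0.6 = 3.6. With 15 per arm, a distorted ratio would often not reach significance, but it would stand in the AE table.

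**3. Timing of the last check.** If week 12 is counted from treatment start, it ends on day 12 × 7 = 84, and ±3 days gives days 81 to 87. Sessions still to come, over all seven positions of the weekly rest day:
- Visit on day 81 after that day's session: 2 or 3 of 72 (2/72 = 2.8%; 3/72 = 4.2%).
- Visit on day 81 before that day's session: at most 4 of 72 (5.6%).
- Visit on day 84: none, or 1 if held before that day's session.
- Visit on days 85 to 87: none.

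A visit in the early part of the window therefore does not fit section 2.25, which places the second safety test after treatment.

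**The case against.** The strongest reply is that a reader can infer more from these passages than they say. Six points bear on this.

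- **Controls unobserved between visits.** This is an inference. Section 2.18 says the different groups are treated six times a week, controls may receive symptomatic treatment, and section 2.14 recruits inpatients as well as outpatients. The point stands as a limit: one can say only that no comparable contact is described. The frequency sentence sits badly with a once-daily oral drug and needs reconciling.
- **A biased safety comparison.** Section 2.25 names no between-arm AE test, and the question wording may be in the CRF or operating procedures, which are not shown. So the supported wording is that a contrast is liable to bias, not that it is biased. The imbalance in contact, however, comes from the design the article itself describes, and prompt CRF recording (section 2.26) would tend to favour the arm seen daily.
- **Recording closes at the week-12 visit.** No section says so. The definition runs over the whole trial, so later events remain recordable. What is missing is any later scheduled enquiry.
- **The window is symmetric.** A later visit meets section 2.25, so the conflict arises only for early visits. Section 2.21 also words the last time point as 12 weeks after treatment. Read literally, that would remove the early-visit problem, but Table 1 places the point within the treatment period.
- **The detection rates are invented.** They are. They show direction and sensitivity, not size.
- **The direction is conservative.** The bias would overstate harm from the experimental treatment rather than hide it. That is true, but it would still misattribute shared drug effects to the procedure.

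**Conclusion.** The point holds in a limited form. A no-threshold AE definition, unblinded treatment and 72 sessions described for one arm only make any between-arm contrast of AE counts liable to overstate harm in the experimental arm. The size cannot be derived from the document; the ratios of 1.5 to 3.0 rest wholly on assumed detection rates and on controls having no other regular contact.

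The timing point is minor and conditional. It needs week 12 to be counted from treatment start and the visit to fall early in its window. At worst 2 to 3 sessions, or 4 if the visit precedes that day's session, out of 72 come after the last scheduled AE and safety check.

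The document does not support saying that controls go unwatched, that a safety comparison is already biased, or that late events are lost.

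**What to change.** 1. Base any between-arm AE comparison on one scripted question with the same look-back, put to both randomised arms at the existing week 4, 8 and 12 visits.
2. Have it asked by existing study staff who do not rate outcomes, or only after the ratings are complete. A complaint of scalp pain would otherwise reveal the arm to the evaluator scoring MoCA, WMS-IV and FIM.
3. Tabulate events noted during needling or training sessions separately, as procedure events of the experimental arm.
4. Hold the whole week-12 visit, including AE and safety collection, 0 to 3 days after the last session. Controls, for whom no sessions are described, would be seen on the matching calendar days, 84 to 87.
5. Reconcile the six-times-a-week sentence in section 2.18 with the control regimen in the same section, and the wording of the last time point in Table 1 with that in section 2.21.

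**Cost:** one CRF question at existing visits, a second AE table and a one-sided window. Moving the whole visit avoids splitting it from the scales, laboratory tests and fMRI, so no extra visits are needed. Visits become slightly longer, and scheduling at week 12, including the scan, is less flexible.

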### Data management

2.26

All information of participants will be truthfully, completely, accurately, and timely recorded in CRFs, and codes and initials will be used to replace the information of participants. Special personnel will be asked to manage the relevant data, and each participant's personal information will be kept strictly confidential. Without the explicit permission of the person in charge of the research group, data will not be shared with third parties other than data recorders and data administrators. At the end of the trial, researchers will submit the CRFs on time, and then, the quality control team members will check the completeness and accuracy of the CRFs.

